**High dose oral rifampicin arm (R35PO)**

Oral rifampicin at 25mg/kg for 8 weeks, in addition to standard fixed dose combination quadruple antituberculous tablets containing ~10mg/kg of rifampicin, will be administered for the first 8 weeks. Fixed-dose combination tablets according to weight bands as presented (
Table 3) will be dispensed with additional 300mg oral rifampicin tablets to make the rifampicin dose up to ~35mg/kg/day. All study drugs will be taken orally during this period (either as intact tablets or via nasogastric tube). Study drugs will be administered under directly observed therapy by nursing staff whilst the participant remains in hospital. After discharge study drugs will be dispensed to participants at the week 4 visit. Fixed dose combination antituberculous therapy will be prescribed through routine care pathways initially via the hospital and subsequently via linked TB clinics according to National Guidelines. Participants will be weighed at each visit and TB drug dose will be adjusted as necessary. At the end of the intervention period (week 8) the participant begins standard of care continuation phase TB treatment (
Table 4).

**Table 3. T3:** Daily administration of oral rifampicin during the first 8 weeks in the high dose oral rifampicin arm (R35PO) and week 2–8 in arm R20IV.

Weight	Number of RHZE tabs (150/75/400/275 mg)	Additional rifampicin 300mg tablets	Total rifampicin dose (mg)
30–37 kg	2 tabs	3 tabs	1200
38–54 kg	3 tabs	4 tabs	1650
55–70 kg	4 tabs	5 tabs	2100
≥ 71 kg	5 tabs	6 tabs	2550

**Table 4. T4:** Daily number of fixed dose tablet in the control arm (arm R10PO) during week 0–8 and for all arms during the continuation phase of treatment.

Weight	Intensive Phase (week 0–8)	Continuation Phase (month 3–12)	
	RHZE fixed dose combination daily (150/75/400/275 mg) ^3^	RH (150/75) ^3^	RH (300/150) ^3^
30–37 kg	2 tabs	2 tabs	
38–54 kg	3 tabs	3 tabs	
55–70 kg	4 tabs		2 tabs
≥ 71 kg	5 tabs		2 tabs

**Control arm, standard of care arm (R10PO)**

The control arm will receive standard of care TB treatment: Oral rifampicin ~10 mg/kg, isoniazid ~5 mg/kg, pyrazinamide ~25 mg/kg, ethambutol ~20 mg/kg in fixed-dose combination tablets according to weight bands for 8 weeks (
Table 4). Participants will receive intact tablets or via nasogastric tube. Fixed dose combination antituberculous therapy will be prescribed through routine care pathways initially via the hospital and subsequently via at TB clinics according to National Guidelines.

***Pharmacokinetic sampling.*** Intensive plasma PK sampling will take place on day 2(+/-1) at hours 0, 2, 4 and 8 post dose as well as a single CSF sample. Where possible a single plasma and CSF sample will be collected on day 14 (+/- 2 days).

***Blood test monitoring.*** Routine blood monitoring will take place on days 1, 3, 7 and 14, week 4 and week 8 to monitor for any rifampicin-related toxicity (
Table 5 and
Table 6).

**Table 5. T5:** In-patient schedule of events.

Study visit	Screening	Enrolment D1	Day 2	Day 3	Day 7	Day 10	Day 14	Further Hospitalization
Visit window (days)			±1	±1	±1	±1	±2	
Screening Consent	X							
Assess eligibility criteria		X						
Informed enrolment consent		X						
Clinical history and examination								
Past medical history	(X)							
Medication review	(X)	X	X	X	X	X	X	X
Document HIV status	(X)							
Current symptoms	(X)	X	X	X	X	X	X	X
Examination	(X)	X	X	X	X	X	X	X
GCS score	(X)	X	X	X	X	X	X	X
BMRC disease grade		X	X	X	X	X	X	X
Adverse events assessment ^b^		X	X	X	X	X	X	X
Investigations								
HIV-test (if not known positive)	(X)							
Cryptococcal antigen	(X)							
Sodium/Potassium	X ^i^	X ^i^			X		X	X
Glucose (bedside)	(X)							
Creatinine ^h^	X ^i^	X ^i^			X		X	X
Hepatic panel ^a^	X ^i^	X ^i^		X	X		X	X
Blood Count (including differential)	X ^i^	X ^i^			X			X
CD4 count if HIV-positive	X ^i^	X ^i^						
Pregnancy test	Women							
CSF sample (aim >10ml, as per SOP ^c^)	(X)		X ^d^	as clinically indicated (storage of remaining specimen)			X (Paired plasma)	X (as clinically indicated)
Plasma PK sampling 0, 2, 4, 8 hrs			X					
Sparse plasma PK (one sample)							X	
Chest radiograph	(+/-)							
CT head ^f^	+/-	+/-						
Abdominal Ultrasound Scan		X						
Urine sample ^g^	(X)							
Blood/DNA/RNA storage		with consent						with consent
Approx. volume blood (mL)	0	20	20	3	7	0	7	7

**()**= part of routine medical care
**^a^ Hepatic panel** = alanine aminotransferase (ALT), alkaline phosphatase (ALP) and bilirubin. Hepatitis BsAg, Hepatitis C Ab and INR will be added if baseline ALT is elevated. In the event of DILI hepatic panel will be performed more regularly.
**^b^ Adverse events** will be recorded according to DAIDS toxicity scale
**^c^ SOP** = standard operating procedure detailing exact processing and testing algorithm of CSF
**^d^ CSF PK** will be timing randomised to early (2–4hrs) or medium (4–6hrs) or late interval (6–8hrs) post dose.
**^f^ Contrast enhanced CT head** is indicated if there is focal neurology at baseline or during enrolment period
^g^
**Urine** sample may be collected for testing with LAM (lipoarobinmannan) or urine Xpert MTB/Rif Ultra as part of TB work-up
^h^ Additional
**renal monitoring** will be undertaken in those with abnormal baseline creatinine
^i^
**Baseline bloods** must occur at either screening or enrolment visit. It is likely these visits will be on the same day. If baseline bloods were done at screening and enrolment occurs >48 hours later baseline blood tests will be repeated.

**Table 6. T6:** Out-patient schedule of events.

Study visit	Week 4	Week 8	Week 12	Week 18	Week 24	Sick Visit
Visit window (weeks)	±1	±1	±1	±2	±2	As needed
Dispensing of study drug		X	standard fixed dose therapy til 12 months as per local guidelines			
Interim history	X	X	X	TELEPHONE CONSULTATION OR IN PERSON	X	X
Adverse events assessment	X	X	X		X	X
Medication review	X	X	X		X	X
Examination	X	X	X		X	X
Modified Rankin score		X			X	
Detailed neurocognitive follow-up		X			X	
Center for Epidemiological Studies of Depression Scale (CES-D)		X			X	
Sodium, potassium						X (if clinically indicated)
Creatinine						X (if clinically indicated)
Hepatic Panel ^a^	X	X				X (if clinically indicated)
FBC, differential ^b^						X (if clinically indicated)
Storage bloods ^c^		X				X (IRIS event only)
CSF with storage						X (if clinically indicated)
ART counselling ^d^	X	X				
Commence/switch ART ^d^		X				
Total volume of blood (ml)		20				20

^a^Hepatic panel = ALT, ALP, bilirubin +/- INR

^b^FBC; full/complete blood count

^c^Blood will be collected and stored for research if storage consent has been received, refer to site SOP.

^d^HIV-infected patients not receiving effective ART, ART counselling to be performed by qualified counsellors as per standard clinic procedures. Physician discretion allowed for timing of ART initiation.

***Neurocognitive assessment.*** Where possible a detailed neurocognitive assessment will take place on week 8 and week 24.

***Antiretroviral therapy.*** HIV-positive participants who are ART naïve or who have defaulted ART will initiate ART after completion of the intensive phase of TB treatment (at week 8) in accordance with WHO and Ugandan guidelines. An efavirenz-based regimen or dose-adjusted (twice daily) dolutegravir-based regimen would be used in accordance with Ugandan HIV treatment guidelines (currently under revision)
^32^. Participants who were enrolled on a failing efavirenz-based regimen will be switched at week 8 to a dose-adjusted dolutegravir-based regimen. Current protease inhibitor or nevirapine-based ART is an exclusion criteria so we do not anticipate having participants on these agents. All participants will be registered at the Infectious Diseases Institute HIV clinic or the Mbarara Hospital HIV clinic such that their HIV care lies within the national HIV service framework.

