### Hypotheses

Our
**primary hypothesis** is that intravenous rifampicin (20mg/kg) and high dose oral rifampicin (35mg/kg) will result in significantly increased plasma and CSF exposure during the critical early days of TBM treatment as compared to standard control (10mg/kg oral rifampicin).

Our
**secondary hypotheses** are that high dose rifampicin will lead to improved early mycobacterial clearance from the CNS, reduced inflammatory response, and thereby will result in more rapid resolution of coma, improved long-term functional status, reduced TBM immune reconstitution inflammatory syndrome (IRIS) incidence and lower mortality.

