### Endpoints

***Primary end points***

*1. Pharmacokinetic parameters*

Plasma and CSF rifampicin area under the curve (AUC
_0-24h_), and maximum concentration (C
_max_)

*2. Adverse events*

We will use a composite safety endpoint for the 8-week intervention period that includes clinical grade 3-5 adverse events (AEs) (as classified by Division of AIDS (DAIDS) Toxicity Scale) or all serious adverse events (SAEs), drug-induced liver injury (DILI), grade 3-5 defined by alanine transaminase (ALT) >5x upper limit of normal (ULN), or discontinuation of rifampicin for >5 consecutive days in the first 8 weeks for any cause.

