***Primary analysis***

**Pharmacokinetic analysis**

The following pharmacokinetic parameters will be calculated using standard two-stage approach involving calculation of pharmacokinetic parameters in those patients in whom a full PK curve was recorded:

1. C
_max_ - the peak concentration of the drug after administration2. T
_max_ - the time to reach C
_max_

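### The only primary PK method stated, a two-stage calculation in patients with a full curve, cannot give CSF AUC0-24h or CSF Cmax from one CSF sample per participant

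*Protocol article*

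**What the plan says.** All references are to the protocol article.

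- **Hypotheses.** The primary hypothesis is that both high-dose regimens "will result in significantly increased plasma and CSF exposure during the critical early days of TBM treatment", compared with standard dosing.
- **Primary end points, item 1.** The parameters are "Plasma and CSF rifampicin area under the curve" over 0–24 h, and the maximum concentration.
- **Pharmacokinetic sampling.** On day 2 (±1 day) plasma is drawn "at hours 0, 2, 4 and 8 post dose as well as a single CSF sample". At day 14 (±2 days) one further plasma sample and one further CSF sample are taken, if feasible.
- **Table 5, footnote d.** The timing of the day-2 CSF sample "will be timing randomised to early (2–4hrs) or medium (4–6hrs) or late interval (6–8hrs) post dose".
- **Primary analysis, Pharmacokinetic analysis.** Cmax, Tmax, AUC0-24 and time above MIC come from a standard two-stage approach "involving calculation of pharmacokinetic parameters in those patients in whom a full PK curve was recorded". No exception or separate method is given for CSF.
- **Secondary analysis.** A population PK-PD model is planned to relate rifampicin exposure (Cmax and AUC0-24h) to survival, recovery of consciousness and functional status.

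**The concern.** A two-stage analysis first computes each parameter within each participant and then compares those values between arms. The first step needs several concentrations from one dosing interval in the same person. Plasma has four on day 2 and CSF has one.

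The stated endpoint, sampling schedule and method therefore do not fit together for CSF. This matters because CSF exposure is half of the primary hypothesis, and the article says the pharmacokinetic results will guide which regimen goes to phase III. If the CSF measure is not fixed in a computable form, the investigators will have to choose it and its model later, possibly after seeing data from an open-label trial.

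**Working it through.** This is mainly a comparison of the stated endpoints, samples and method. One stated figure can be reproduced first.

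**1. The stated power.** Inputs from Sample size: 15 per group, log-scale difference 0.54, SD 0.36 (control) and 0.48 (experimental), two-sided alpha 0.05, unequal-variance t-test.

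- Standard error = √(0.36²/15 + 0.48²/15) = √(0.1296/15 + 0.2304/15) = √0.024 = 0.155.
- Noncentrality = 0.54/0.155 = 3.49, with Satterthwaite df of 26.0.
- Power = 91.8%, against a stated 90%. The figure reproduces.

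This calculation is for log Cmax and takes one Cmax value per participant as its unit. The section does not say whether it refers to plasma or CSF.

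**2. Parameters and samples on day 2.**

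| Primary parameter | Samples per participant | Derivable within participant? |
|---|---|---|
| Plasma Cmax | 4 (0, 2, 4, 8 h) | Yes, as the highest observed value |
| Plasma AUC0-24h | 4 (0, 2, 4, 8 h) | Yes, with extrapolation beyond 8 h |
| CSF Cmax | 1 (random window, 2–8 h) | No: a concentration at one time, not a peak |
| CSF AUC0-24h | 1 (random window, 2–8 h) | No: one point defines no area |

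Two of the four named parameters are affected.

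**3. Does day 14 help?** No. It is one optional sample about 12 days later, in a different dosing interval. In the intravenous arm its window also spans the planned change of route after 14 days. Two single samples so far apart do not make one curve.

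**4. Participants who qualify.** A full CSF curve is planned for no one, so the number eligible for a two-stage CSF parameter is 0 of 60.

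**5. What the CSF data can support.** Up to 60 day-2 CSF concentrations at randomised times, each with same-day plasma, form a sparse design that can be pooled across participants. With 20 per arm and three windows, an even split gives 20/3, or 6–7 per arm per window. Comparing arms separately within a window would be weak. If the difference and SDs in step 1 carried over to CSF, which the article does not say, power would be about 51% with 6 per arm and 58% with 7. All windows should therefore be analysed together, with time in the model.

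**6. Is a pooled method assigned to this endpoint?** No. The population model appears only under Secondary analysis, for exposure-response. Statistical methods adjusts all analyses for site, BMRC grade and baseline predictors of missingness; CSF sampling time is not in that list.

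**The case against.** The strongest defence has two parts.

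First, the paragraph that limits the calculation to full curves never mentions CSF. It may have been written with the intensive plasma sampling in mind, and a separate analysis plan, to which the article refers, may give the CSF method. This softens the point but does not remove it. The paragraph is the only primary PK method stated, it lists the same parameters as the primary endpoints, and it makes no exception for CSF. An analysis plan that used a pooled model for CSF would depart from this text rather than just add detail to it.

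Second, randomising the CSF time is a recognisable sparse-sampling design, and a population model is already planned. That is correct. A reader might infer that the CSF endpoint has no analysable data; the documents do not support that. The fault is in the assigned method.

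Three other stronger readings should also be resisted:

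- A reader might count arm-by-parameter contrasts and say that half of the primary tests fail. The article lists no such set of tests; Sample size describes two comparisons at 5% each.
- A reader might infer that a single CSF value reflects sampling time as strongly as dose. Nothing in the documents measures this. Because timing is randomised, it should mainly add variance and chance imbalance, not systematic bias between arms.
- A reader might extend the point to plasma AUC0-24h because sampling stops at 8 h. That parameter can be computed by extrapolation. How much of it lies beyond 8 h depends on absorption rate and half-life, which the article does not fix. It is a separate question.

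**Conclusion.** The point holds as a conflict within the article. CSF AUC0-24h and CSF Cmax, two of the four named primary PK parameters, cannot be obtained by the only primary PK method stated, and 0 of 60 participants would qualify for them under it. The conclusion rests on applying the full-curve rule to CSF, as the text does by making no exception. If the rule was meant for plasma alone, the article states no primary derivation for CSF, and the same passages still need reconciling.

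The planned CSF samples remain usable and the plasma parameters are not in question. Because CSF exposure is part of the primary hypothesis, the correction should be made before the data are analysed.

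**What to change.** For CSF, drop the full-curve two-stage rule and choose one of the following as primary:

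- **(a)** Keep CSF AUC0-24h and Cmax, and name a joint plasma-CSF population PK model, using all CSF samples with their actual times post dose, as the primary derivation.
- **(b)** Redefine the primary CSF endpoint as day-2 log CSF rifampicin concentration, compared between each high-dose arm and control in a model with sampling window (or actual time post dose), site and BMRC grade.

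Make Primary end points, Pharmacokinetic analysis and the analysis plan agree on the choice. Under (a), state separately that the model serves the primary endpoint as well as the secondary exposure-response work.

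The cost is a change of wording in the endpoint and analysis sections. No further lumbar punctures or blood samples are needed. The small downside is that CSF exposure becomes a model-based estimate under (a), or a timed concentration under (b), rather than a parameter observed in each participant.

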### Randomisation and treatment allocation

Adults who have given consent for, and undergone, a diagnostic screening lumbar puncture and are eligible for enrolment will then be approached for enrolment consent after which they will be randomised. Randomisation will occur at study entry and must occur prior to the 4th dose of TB treatment. Participants will be randomised by a computer generated permutated block randomization algorithm of different sized blocks with a 1:1:1 randomization ratio into the three arms described above.

Randomisation will be stratified by:

1. Clinical site2. British Medical Research Council (BMRC) TBM disease grade I or II/III at time of consent

All randomised participants will initiate their allocated study TB treatment within 24 hours of randomisation, and preferably the same day. As TBM is a medical emergency, initiation of standard of care TB treatment will not be delayed whilst waiting for randomisation.

***Treatment discontinuation***. Due to the urgent need to begin TBM therapy to reduce mortality, enrolment will not be delayed whilst waiting for enrolment blood test results and participants will be replaced
*a posteriori* if baseline ALT>3x ULN. As infection with a rifampicin resistant TB strain is an exclusion criterion, all patients in whom rifampicin resistant TB is identified after randomisation may have their treatment altered as per physician judgement. Once randomised, analysis is by modified intent-to-treat (ITT).

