***Antituberculous therapy***

**Intravenous rifampicin arm (R20IV)**

For the first 14 days study drug will be administered as intravenous rifampicin 20mg/kg once daily. Study medications will be dispensed during hospitalization to ward staff who will administer the drugs to the participants under directly observed therapy. Rifampicin 600mg will be reconstituted with 10 ml of sterile water for a dilution of 60 mg per ml of reconstituted solution. The weight-specific volume of rifampicin solution will be drawn up (
Table 1) then further diluted in 500 ml 5% Dextrose solution. The solution will be administered as a continuous infusion via a peripheral venous catheter over 2 hours. Thereafter the line will be flushed with 5 ml 0.9% normal saline after which the cannula will be capped. Other antituberculous drugs (isoniazid, pyrazinamide and ethambutol) will be given orally by weight (
Table 2) as intact tablets unless they are unable to swallow voluntarily, e.g. in participants with a depressed level of consciousness, in which case tablets will be crushed and given via nasogastric tube.

**Table 1. T1:** Intravenous administration of rifampicin by weight for day 0–14 in the intravenous rifampicin arm (arm R20IV).

Weight (Kg)	Rifampicin dose (mg)	SUSPEND RIFAMPICIN IN EACH VIAL (600MG) IN 10MLS OF WATER FOR INJECTION	Volume used (mL)	Number of vials used	DILUTE IN 500MLS OF 5% DEXTROSE AND ADMINISTER OVER 120 MINUTES
28.5 – 31.49	600		10	1.0	
31.5 – 34.49	660		11	1.1	
34.5 – 37.49	720		12	1.2	
37.5 – 40.49	780		13	1.3	
40.5 – 43.49	840		14	1.4	
43.5 – 46.49	900		15	1.5	
46.5 – 49.49	960		16	1.6	
49.5 – 52.49	1020		17	1.7	
52.5 – 55.49	1080		18	1.8	
55.5 – 58.49	1140		19	1.9	
58.5 – 61.49	1200		20	2.0	
61.5 – 64.49	1260		21	2.1	
64.5 – 67.49	1320		22	2.2	
67.5 – 70.49	1380		23	2.3	
70.5 – 73.49	1440		24	2.4	
73.5 – 76.49	1500		25	2.5	
76.5 – 79.49	1560		26	2.6	
79.5 – 82.49	1620		27	2.7	
82.5 – 85.49	1680		28	2.8	
85.5 – 88.49	1740		29	2.9	
88.5 – 91.49	1800		30	3.0	

**Table 2. T2:** Daily number of tablets of isoniazin, pyrazinamide and ethambutol by weight during the first 14 days for the intravenous rifampicin study arm (arm R20IV).

Baseline weight (kg)	ISONIAZID 100 mg*	PYRAZANAMIDE 500 mg*	ETHAMBUTOL 400 mg
≤30–33	1.5	1.5	1
34	1.5	1.5	2
35–44	2	2	2
45–54	2.5	2.5	2
55	3	3	2
56–64	3	3	3
65	3	3.5	3
≥66	3.5	3.5	3

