After 14 days of intravenous rifampicin the participant will be switched to high dose oral rifampicin (35mg/kg) for the remaining 6 weeks of the intervention period administered as per the participants in the high dose oral rifampicin arm.

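### The day-14 (±2) plasma and CSF sample straddles the intravenous arm's switch to oral rifampicin, so a by-arm summary of it would mix two regimens in arm A

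*Protocol article*

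**What the plan says.** All quotations are from the Protocol article.

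- **Late sample.** Under Pharmacokinetic sampling: "Where possible a single plasma and CSF sample will be collected on day 14 (+/- 2 days"). Table 5 repeats the ±2 days, applies it to every arm, and labels enrolment as D1.
- **Intravenous period.** In the text on arm R20IV: "For the first 14 days study drug will be administered as intravenous rifampicin 20mg/kg once daily", then "After 14 days of intravenous rifampicin the participant will be switched to high dose oral rifampicin (35mg/kg) for the remaining 6 weeks" of the intervention, given as in the high-dose oral arm.
- **Labels for the same periods.** The caption of Table 1 reads "Intravenous administration of rifampicin by weight for day 0–14 in the intravenous rifampicin arm". Table 3 gives the oral period as "week 2–8 in arm R20IV".
- **Start of dosing.** Under Randomisation and treatment allocation: "All randomised participants will initiate their allocated study TB treatment within 24 hours of randomisation, and preferably the same day".
- **Early sampling.** "Intensive plasma PK sampling will take place on day 2(+/-1) at hours 0, 2, 4 and 8 post dose", with a single CSF sample.
- **Use of the data.** The two-stage calculation is confined to participants with a full concentration curve (Pharmacokinetic analysis). The Sample size section says that the two investigational arms will be compared mainly descriptively.

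**The concern.** The window reaches two days either side of day 14, and arm A changes regimen at about day 14. A sample taken early in the window reflects intravenous 20 mg/kg. One taken late can reflect oral 35 mg/kg, which is arm B's regimen. Arms B and C have no such change, so the mixing occurs in one arm only.

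The sample has some weight. It is the only scheduled exposure measurement beyond the first days, and the second of two scheduled pharmacokinetic CSF samples per participant. The Introduction places steady state beyond 7 days of therapy, so this is the only planned draw in that period. The Discussion says that the data will help to define both dose and route for a phase III trial and that a bioequivalent oral dose is a priority. Post-switch samples counted as arm A would make the two routes look more alike than they are.

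**Working it through.** **1. The plan's own pharmacokinetic figure.** The Sample size section gives 90% power with n = 15 per group, a log-scale difference of 0.54, SDs of 0.36 and 0.48, and a two-sided unequal-variance t-test at 0.05.

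- Standard error = √(0.36²/15 + 0.48²/15) = √0.024 = 0.155.
- Noncentrality = 0.54/0.155 = 3.49, with about 26 Satterthwaite degrees of freedom.
- Power = 91.8%, which agrees with the stated 90%.

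This figure concerns log Cmax against control. It does not use the day-14 sample and does not change under anything below.

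**2. Day count.** The window is 14 − 2 to 14 + 2, i.e. days 12, 13, 14, 15 and 16. With 14 daily intravenous doses, last intravenous day = first dosing day + 13.

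| Reading of the day numbering | Last intravenous day | Window days after the switch | Share |
|---|---|---|---|
| First dose on D1 (Table 5 numbering) | 14 | 15, 16 | 2/5 = 40% |
| 14 doses counted from day 0 | 13 | 14, 15, 16 | 3/5 = 60% |
| First dose on day 2 (24 h after randomisation on D1) | 15 | 16 | 1/5 = 20% |
| Table 1 label taken literally (days 0 to 14) | 14 | 15, 16 | 2/5 = 40% |

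Table 3's label is read as elapsed weeks, because Table 4 counts the intensive phase from week 0. On that reading, oral dosing starts once two weeks have passed. The Table 1 label covers 15 calendar days against 14 in the text, so the labels themselves do not agree. Every row leaves at least one permitted day after the switch.

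**3. Effect on a by-arm summary.** Let f be the share of arm A late samples taken after the switch, and δ the true intravenous-oral difference in mean log concentration. If post-switch samples have arm B's mean:

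expected observed difference = (1 − f)·δ.

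With sampling even over the five days, f equals the share in the table:

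- f = 0.2: 80% of δ remains, a shrinkage of 20%.
- f = 0.4: 60% remains, a shrinkage of 40%.
- f = 0.6: 40% remains, a shrinkage of 60%.

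For scale only, take δ = 0.54. The protocol uses this value for the comparison with control and gives none for intravenous against oral. The difference would then show as 0.43, 0.32 or 0.22.

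**The case against.** The strongest reply is that the sample hardly matters to what the trial sets out to show. Most of this stands.

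- **Primary analysis.** A reader might infer that the primary pharmacokinetic endpoint is contaminated. The document does not support that. The two-stage calculation takes only full curves, and the only full curve is on day 2 (±1). One optional draw cannot yield Cmax or AUC. The primary hypothesis concerns the early days against control.
- **Intravenous-oral contrast.** It is descriptive and also has the day-2 data, which lie wholly in the intravenous phase. The article states no by-arm day-14 comparison, so the harm is conditional on one being made.
- **Size.** A reader might take 40% as the expected shrinkage. It is one case of several. The Data collection section keeps participants in hospital for the first 14 days, which may favour draws on or before day 14, although Table 5 allows for further hospitalisation. A draw on the first oral day before the oral dose still reflects the last intravenous dose. The true share cannot be known from the document.
- **Recoverability.** A reader might infer that mixed samples are lost to analysis. That goes too far. Inpatient dosing is directly observed in both high-dose arms, medication is reviewed at day 14, and the planned population pharmacokinetic-pharmacodynamic model could use actual dosing and sampling times.

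It can also be said that a condensed article leaves sample classification to fuller documents. That is fair for classification. The window and the switch, however, are both stated here and they overlap. No later analysis turns a post-switch sample into an intravenous-phase one; it can only set it apart, with at most 20 participants per arm and fewer after early deaths.

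**Conclusion.** The overlap is real under every reading of the day numbering examined: 1 to 3 of the 5 permitted days fall after the arm A switch. Its reach is limited to the late plasma and CSF sample and to any by-arm summary of that sample, where the intravenous-oral contrast would be pulled towards zero. The range of 20% to 60% rests on two assumptions that the document neither states nor rules out: even sampling over the window, and post-switch samples equal to those of arm B. The stated 90% power, the two-stage parameters and the comparisons with control stand. This is a cheap improvement worth making, not a fault in the primary analysis.

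**What to change.** 1. Reconcile the descriptions of the intravenous period (arm text, Table 1, Table 3) with one another and with the visit-day numbering of Table 5, so that the sampling window can be read against the switch. This point takes no position on which dosing schedule is right.
2. In arm A only, require the late plasma and CSF sample to follow an intravenous dose and to precede the first oral dose. Leave the ±2-day window unchanged in arms B and C, which have no switch, so that no valid samples are lost there. Cutting the window to days 12–14 would not be secure: if 14 doses are counted from day 0, day 14 is already after the switch.
3. Record the time and route of the preceding rifampicin dose with each late sample.
4. Report any post-switch arm A sample separately, by the route of the preceding dose.

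The cost is a few lines of wording and two data items. A few optional arm A samples may be lost or fall outside the permitted period. No dose, treatment rule or sample-size figure changes.
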